#### **4.4.14 Feasibility of a larger study**

##### **4.4.14.1 Feasibility criteria**

The feasibility criteria for a larger study are defined as follows:

- a) a target recruitment rate of 40% of 85 eligible patients (or 4-5 participants per month); the total number of eligible PD patients was estimated based on the number of eligible PD patients treated at RZM in the last 3 years.
- (b) a target retention rate of 80%,
- (c) a minimum target adherence rate of 75% (at least 3 out of targeted 4 practice sessions per week; documented in the CRF).
- (d) high safety of the intervention, no severe side effects or only very mild and transient side effects (continuously collected by means of UE log in CRF; see also chapter 4.5.2)
- (e) high acceptance of the intervention, continuously evaluated narratively during the intervention period and through focus groups with semi-structured questions (see chapter 4.4.14 and CRF for a detailed description of the focus groups and the questions asked).

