#### **4.1.2.3 Number of participants and sample size**

For this study, 34 people with Idiopathic Parkinson's Syndrome will be included. Of the 34 people with Parkinson's disease, 17 will be randomised to intervention group 1 and 17 to control group 2.

According to Julious, participants per group are considered a minimum sample size for a pilot study. (Julious, 2005) while Browne specifies a number of participants of 30 for a two-arm study. (Browne, 1995). Therefore, to evaluate the feasibility criteria and preclinical effects of the experimental intervention compared to the conventional control intervention, a sample size of 34 is aimed for, based on 30 participants, including an expected failure rate of 10% and using the formula  $N = n / (1 - (z/100))$ . Here, n is the number of participants (30) and z is the expected failure rate (10%).

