#### **4.5.1.2 Side effect (NW)**

An adverse event (AE) is any adverse event, as defined above, for which there is causality to the study intervention.

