#### **4.5.1.4 Severity**

The severity levels of the incidents ((S)UE and (S)NW) are defined as follows:

- Mild - Intervention must be interrupted due to the incident, but can be continued the same day or the following day. Consultation with a doctor for treatment is not necessary;
- Moderate - Intervention must be interrupted, can be continued on another day but not immediately the following day. Consultation with a doctor for treatment is necessary.
- Severe - The intervention must be terminated and cannot be continued due to the event (in terms of a drop-out according to chapter 5.4)

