## 5.6 Data analysis

### 5.6.1 Statistical data analysis

Statistical data analysis is performed using IBM SPSS software, version 26.0 (IBM Corporation, Armonk, NY, USA) and Tobii Pro Lab Analyser (Tobii, Danderyd, Sweden). The statistical significance level is defined by a p-value of  $<0.05$ . An attempt is made to avoid missing data by inspecting the questionnaires after completion and, in case of unanswered items, asking the study participants to complete them. The number of missing data is noted; due to the less sensitive topic of the study, it is assumed that missing variable values can be assigned to "missing completely at random" or "missing at random". An intention-to-treat analysis is performed for all cases analysed in their originally assigned group.

Descriptive statistics are used for demographic data and primary and secondary outcomes. Counted and nominal scaled data (gender, fall rate, recruitment, retention and adherence rate, number of missing data if applicable, number of adverse events) are reported as whole numbers or percentages. Ordinal scaled variables (MMSE, UPDRS, H & Y, FGA, BBS, PDQ-39, FOGQ, FES-I, BDI-II) are expressed as median (minimum, maximum or interquartile range) and metric variables (TUG, TUGman, FSST, 10MWT, eye movements: Saccade velocity, amplitude, latency, fixation duration) by mean (95% confidence interval, CI or standard deviation, SD). The data is also presented graphically (e.g. by bar charts, box plot or line graphs).

The eligibility rate (%) is the percentage of patients suitable for the study after applying the inclusion and exclusion criteria from the Parkinson's patients treated at the Reha Zentrum Münster during the study period.

The recruitment rate (%) is determined as follows:  $(N_{\text{Consent}}/N_{\text{eligible}}) \times 100$ ; where  $N_{\text{Consent}}$  is the number of participants who signed the informed consent form;  $N_{\text{eligible}}$  is the number of patients eligible for the study based on the inclusion and exclusion criteria.

The retention rate (%) is calculated as follows:  $(N_{\text{completed}}/N_{\text{Total}}) \times 100$ ; where  $N_{\text{completed}}$  is the number of participants who completed the study;  $N_{\text{Total}}$  is the total number of participants in the study.

Adherence rate (%) is determined as follows: (Actual number of exercise sessions/planned number of training sessions)\*100 (Osterberg & Blaschke, 2005).

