Eligibility, recruitment and adherence rates are calculated using the Wilson 'score' method propagated by Newcombe together with its 95% CI (Newcombe, 1998). In the case of a proportion close to 0 or 1, a Poisson approximation according to Brown is used. (Brown, Cai, & DasGupta, 2001)..

A test for statistically significant differences between the groups at baseline: for nominal data the Fisher's Exact Test is used, for ordinal data the Mann Whitney-U test and for metric data the T-test for independent samples. A preliminary inferential statistical analysis to detect trends in the effectiveness of the intervention and as a basis for sample size calculation for a randomised controlled trial with sufficient power of at least 80% (based on mean differences (SD) between groups) will be performed. For inferential statistics, metric data are first tested for normal distribution and significant data outliers using the Shapiro-Wilk test, Q-Q plots and histograms. Non-normally distributed data are transformed using suitable transformation (e.g. ln, square root), checked again and analysed non-parametrically if normal distribution is missing.

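### Feasibility criterion (d) reads high safety from seeing no severe side effect, but 17 patients in group 1 can show only that no signal was seen

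*Protocol*

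**What the plan says.** Section 4.4.14.1 of the protocol lists five criteria, (a) to (e), for the feasibility of a larger study. Criterion (d) is "high safety of the intervention, no severe side effects or only very mild and transient side effects". It gives no denominator, tolerated rate or confidence bound.

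The terms are defined in section 4.5.1:

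- A side effect is an adverse event "for which there is causality to the study intervention" (4.5.1.2).
- The top severity grade is "Severe - The intervention must be terminated and cannot be continued due to the event", and such a patient is classed as a drop-out (4.5.1.4).
- A serious incident (death, threat to life, lasting disability, hospital treatment) is defined separately in 4.5.1.3.

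On numbers, section 4.1.2.3 says that "17 will be randomised to intervention group 1 and 17 to control group 2".

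On analysis, section 5.6.1 puts adverse events among the data simply counted: "number of adverse events) are reported as whole numbers or percentages". Intervals are assigned elsewhere: "Eligibility, recruitment and adherence rates are calculated using the Wilson 'score' method", each with a 95% confidence interval. The synopsis adds retention to that list. Both places name a Poisson approximation for proportions near 0 or 1. Adverse events are in neither list.

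**The concern.** Criterion (d) turns an observation (no severe side effect was seen) into a conclusion (the intervention is highly safe). In a group of 17 an empty count is likely over a range of true rates, so it says little about how low the rate is. The planned reporting would not show this, because a count of 0 or a percentage of 0% carries no sign of its imprecision.

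At stake is the sentence that the pilot passes on. A report that follows the plan could justify the larger trial with a safety claim that its data do not support. The problem does not depend on how events are graded and would remain with a perfect severity scale.

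**Working it through.** **Inputs**

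- Planned total: 30 participants inflated for 10% loss (4.1.2.3).
- Group 1: 17 patients (4.1.2.3).
- Event: at least one severe side effect, meaning one that ends the intervention (4.5.1.2, 4.5.1.4).
- Tolerated rate: none stated. The true rates below are assumptions chosen to show a range.

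**1. The plan's own figure.** N = 30 / (1 − 10/100) = 33.3, rounded up to 34, so 17 per group. The figure reproduces. The protocol gives no error rate for criterion (d), so there is nothing further to reproduce.

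**2. Chance of no severe side effect.** With independent patients and a true per-patient rate p, P(0 events in n) = (1 − p)^n.

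| True rate p | n = 17 (group 1) | n = 34 (both groups) |
|---|---|---|
| 1% | 84% | 71% |
| 2% | 71% | 50% |
| 5% | 42% | 17% |
| 10% | 17% | 3% |
| 15% | 6% | 0.4% |
| 20% | 2% | 0.05% |

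For example, 0.95^17 = 0.418.

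**3. How this relates to passing (d).** The second limb of the criterion mentions only very mild and transient effects. If a moderate side effect also fails (d), passing requires no severe event and no moderate event. The values in step 2 are then maximum pass probabilities.

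**4. What an empty count excludes.** The exact upper limit after 0/n is 1 − 0.05^(1/n) one-sided, and 1 − 0.025^(1/n) as the upper end of the two-sided 95% interval.

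- 0/17: 1 − 0.05^(1/17) = 16.2%; 1 − 0.025^(1/17) = 19.5%.
- 0/34: 1 − 0.05^(1/34) = 8.4%; 1 − 0.025^(1/34) = 10.3%.

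The methods that the plan names for other rates give similar values for 0/17. The upper end of the two-sided Wilson interval is 1.96² / (17 + 1.96²) = 18.4%. The Poisson form gives −ln(0.025)/17 = 21.7%. The choice of method does not alter the conclusion.

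**5. Scale.** For a one-sided upper limit of 5% or less, the number of event-free patients must be at least ln(0.05)/ln(0.95) = 58.4, so 59. For 10% or less it is ln(0.05)/ln(0.90) = 28.4, so 29. Group 1 has fewer than either.

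**The case against.** **The missing interval belongs in the SAP.** Whether a proportion carries an interval is commonly settled there, and the SAP is not shown. This stands against the missing interval taken alone. It does not reach the wording of criterion (d), where the protocol itself equates an empty count with high safety.

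**Seventeen is not the stated denominator.** Criterion (d) names none. Section 4.2.1 speaks of the study intervention in group 1 or 2, and section 4.5.1 expects training reactions in both groups. On that reading n = 34, and the chance of an empty count at a 5% rate falls from 42% to 17%. Seventeen is the natural denominator for effects of the added gaze training, but the text does not fix it. Both are therefore shown.

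**Severe is not serious.** A reader might infer that the plan would overlook serious harm 42% of the time. The documents do not support that. The 5% rate is an illustration, severe means termination of the intervention, and serious incidents have their own definition and reporting route. The plan expects 10% loss and sets an 80% retention target, so a 5% termination rate in supervised physiotherapy is not self-evidently unsafe.

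**The upper limit is the edge of the interval.** A reader might take 16% to 20% as a plausible true rate. At those limits an empty count in 17 would occur only 5% and 2.5% of the time, so the criterion would usually detect rates that high.

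**Dropping to 15 patients.** It is tempting to apply the 10% loss and use 0/15. For this endpoint that is wrong: a severe event is itself a drop-out under 4.5.1.4, so removing drop-outs removes the events.

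**Only this criterion lacks a bound.** That would go too far. Criterion (e), acceptance, has none either, and retention has one only in the synopsis.

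**Conclusion.** The point holds as a minor one. Criterion (d) states a conclusion that the planned data cannot support. With no severe side effect among 17 patients, a true rate of up to 16.2% (one-sided) or 19.5% (two-sided) is not excluded. With both groups counted, the limits are 8.4% and 10.3%. At assumed true rates of 2%, 5% and 10%, an empty count in group 1 has a chance of 71%, 42% and 17%.

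This rests on three assumptions: group 1 is the denominator, all 17 are treated and counted, and patients are independent with a common rate. The documents state no tolerated rate, so no single pass probability is the size of the problem.

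The finding does not say that the intervention is unsafe or that the pilot is too small for its purpose. It says only that an empty count should be reported as what it is.

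**What to change.** In section 4.4.14.1(d) and section 5.6.1 of the protocol:

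- Name the denominator as all treated patients, per arm, without removing drop-outs.
- Report per arm the proportion with at least one severe side effect and, separately, with at least one serious side effect, each with an exact (Clopper-Pearson) 95% interval.
- Replace the claim of high safety by a statement that no safety signal was observed, where that is so, and state the rate not excluded. For 0/17 this is 16.2% one-sided, or 19.5% as the upper end of the two-sided interval.

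The cost is a change of wording and one interval per arm for each of the two proportions. The safety statement becomes less favourable. No extra patients or data are needed.

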##### **4.4.14.2 Assessment of safety and side effects**

In order to assess the safety of the participants, the following subjective and objective safety parameters are collected. Subjective parameters are those reported by the participants or asked by the therapists. Examples are general well-being, signs of stress, etc. Constant consultation with the participants regarding these parameters is a standard procedure in the therapy of people with idiopathic Parkinson's syndrome and serves to individually adjust the intensity of the therapy. Objective parameters for assessing safety are those serious or non-serious adverse events that are recorded and evaluated during the study (see chapter 4.5).

##### **Compatibility/ safety parameters**

- Subjective by the participant:  
Through close consultation and feedback with the treating doctor and therapist  
(→ adapt the therapy as the situation requires or as is possible for the participant - usual procedure in every daily therapy routine)
- Objective parameters:  
The recording and evaluation of side effects serves to objectify safety (see chapter 4.5.2).

There is continuous monitoring and assessment of the safety of the intervention to detect adverse events. The detailed procedure is described in chapter 4.5.2.

#### **4.4.14.3 Acceptance of the intervention: focus groups**

A focus group is a form of group interview that focuses on the communication between the participants (Stalmeijer et al., 2014). Through this type of data collection, not only the thoughts and feelings of the participants are collected, but also the background against which they arose. One aim of the focus group is to record, understand and explain the meaning of the beliefs and culture that influenced the participants' feelings, behaviour and attitudes (Rabiee, 2004). Focus groups are particularly well suited to areas that have been little or poorly researched (Kitzinger, 1995). They can also be used to confirm or further support existing data (Stewart et al., 2007).

The questions posed for discussion in the focus groups are listed in the CRF.

#### **4.4.15 Measurement of eye movements during the intervention**

Once a week, at the last therapy session, the eye movements are measured for 12 minutes using Tobii Pro Glasses 3: saccade speed, amplitude, latency and fixation time. This measurement is done after a 5-minute warm-up (warm-up: see Instructor Manual, Appendix 1).

The 12-minute period was chosen because it is expected that the participants will have a familiarisation phase with the Tobii glasses of about 5-6 minutes (communication with Tobii). The data obtained are thus more reliable and closer to reality. Data collection will be done during the performance of standardised exercises to allow for comparison: Exercise 2, 3, 4, 6 and 7.

### **4.5 Adverse events, side effects**

#### **4.5.1 Definitions**

The implementation of the tests and interventions (therapy of the intervention groups) can trigger adverse events and side effects. During the therapy, events such as dizziness, shortness of breath or similar signs of stress may occur as a physiological reaction to stress (the training) in both the intervention group and the control group. In the intervention group, slight eye fatigue may occur, but this can be well controlled by short training sequences, variable exercises as well as breaks and exercises without eye movement training.

#### **4.5.1.1 Adverse event (AE)**

An adverse event (AE) is any adverse occurrence that happens to a subject during participation in this study that is not necessarily causally related to the intervention. This may include illnesses, signs and symptoms that occur after the subject is included in this study or pre-existing illnesses, signs and symptoms that worsen after inclusion in this study.

Pre-existing conditions that do not worsen during the course of the study and adverse events related to concomitant medication are excluded.

#### **4.5.1.2 Side effect (NW)**

An adverse event (AE) is any adverse event, as defined above, for which there is causality to the study intervention.

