### **1.3 Risk-benefit assessment**

The activity-oriented physiotherapeutic programme is basically an evidence-based treatment method based on international guidelines for the rehabilitation of idiopathic Parkinson's syndrome, which is guided by physiotherapists in the course of conventional rehabilitation. This physiotherapeutic measure takes place in both groups to the same extent in addition to the usual inpatient interdisciplinary rehabilitation at the Reha Zentrum Münster. The total amount of training during the rehabilitation stay and its intensity correspond to the cited international guidelines for rehabilitation in idiopathic Parkinson's syndrome. The eye movement training is carried out with the activity-oriented physiotherapeutic programme and is also guided by experienced and trained physiotherapists. Based on clinical experience and literature, it can be assumed that the study participants in the intervention group will benefit at least as much from the treatment as in the standard therapy group.

The intervention is initially carried out in a sitting position in order to achieve habituation to the eye movement training. It is not expected that falls will occur during the intervention as the patients are continuously under physiotherapeutic supervision. Dizziness or eye fatigue could be initially triggered by the training. (Camacho et al., 2019a). This risk is minimised by limiting the duration of treatment to four times 30 minutes per week. Eye movement training will not be performed continuously during the 30-minute period, but intermittently with activity-based training to avoid overload from the outset. The intensity and duration of the interventions are considered low impact. Before, during and after the intervention, any complaints and side

effects are asked about. Since the patients are in the Reha Zentrum Münster for the inpatient rehabilitation stay and the intervention is to be integrated into the daily therapy schedule, there is no additional burden in terms of travel. The expected benefit - the optimisation of treatment and a more efficient rehabilitation - is therefore, according to current medical knowledge, only a low health risk and only a low burden for the patients.

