### 2.3 Study objectives

Thus, four **study objectives** are pursued to deepen the knowledge on effectiveness:

1. Assessment of the effects on dynamic balance (primary endpoint)
2. Investigating the feasibility of a larger randomised controlled trial
3. assessment of the effects on functional mobility with and without manual multi-task, static and dynamic balance, walking speed, health-related quality of life, freezing of gait, fall-associated self-efficacy, depression and fall rate (secondary endpoints).

4. evaluation of the change in eye movements during the intervention, measured once a week in the intervention group over the intervention period.

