| Eye movements during the intervention in group 1: standardised exercises, each at the end of week 1-4, during exercise 2, 3, 4, 6 and 7. | Measured for 12 min: saccade velocity, amplitude, latency, fixation time (Tobii Pro Glasses 3)                            |  |   | X |   |   |
| Abbreviations: Scr=Screening; BL=Baseline; Int.=Intervention period; PI=Post-intervention-; FU=Follow-up- testing.                       |                                                                                                                           |  |   |   |   |   |

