#### 4.3.3.1 Mobile eye-tracking glasses (Tobii Pro Glasses 3)

##### 4.3.3.1.1 Use and application of the mobile eye-tracking glasses

The use and application of the Tobii Pro Glasses 3 eye-tracking glasses is as follows:

Eye-tracking glasses from Tobii AB are used to record the eye movements. The Tobii Pro Glasses 3 carry the CE marking and comply with the applicable health and safety regulations of the European Union. The Tobii Pro Glasses 3 and their handling comply with the following standards:

- EMC Emission: EN55022:2010 Class B, FCC part 15, Class B
- EMC Immunity: EN55024:2010
- SAR EN62311:2008
- Low Voltage Directive 2006/95/EEG
- EMC Directive 2004/108/EC
- Radio and Telecommunications Terminal Equipment Directive (R&TTE) 1999/5/EC
- RoHS Directive 2002/95/EC
- RoHS2 Directive 2006/121/EC
- WEEE Directive 2002/121/EC
- Reach Directive 2006/121/EC
- IEC/EN/UL60950-1:2005 (Electrical safety for global/EU/US)

(ETL Compliance: Conforms to ANSI/UL Std. 60950-1 Certified to CSA Std. C22.2 No. 60950-1; Canadian Compliance Statement: CAN ICES-3(B)/NMB-3(B))

The Tobii Pro Glasses 3 will be worn by the participants for the assessment (items 5, 6 & 10 of the FGA) at all assessment times and during the intervention at the last therapy session from week 1-4 for about 12 minutes each. Before the start of the tests, the participants are informed by the responsible examiners or therapists about the use of the eye-tracking glasses and about possible side effects such as temporary dizziness. The participants will be secured by the physiotherapists at all times. Should this be the case at any time, the examiner or therapist in charge will immediately switch off the glasses and the participants will remove them.

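### Side effects are defined only by causality to the intervention, so reactions to tests or eye-tracking glasses have no class, and in-session glasses dizziness can be attributed either way

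*Protocol*

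**What the plan says.** Section 4.5.1 opens with two kinds of trigger: "The implementation of the tests and interventions (therapy of the intervention groups) can trigger adverse events and side effects". The bracket equates the intervention with the therapy, so the tests are a separate cause. Section 4.3.3.1.1 adds a third: before testing, participants are informed "about the use of the eye-tracking glasses and about possible side effects such as temporary dizziness". Section 1.3 names the same symptom for the therapy itself: "Dizziness or eye fatigue could be initially triggered by the training".

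The operative rules are narrower. Under the heading for side effects, section 4.5.1.2 states: "An adverse event (AE) is any adverse event, as defined above, for which there is causality to the study intervention". (The sentence starts by calling the thing defined an adverse event, which looks like a wording slip.) Section 4.5.1.3 chooses between the SUE and SNW labels by causality to the study intervention. Section 4.5.1.5 defines causality against the intervention only, as does the doctor's assessment in 4.5.2.1.1, and the log items in 4.5.2.1.2 contain one causality item, again for the intervention.

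On who wears the glasses in training, Table 2 in section 4.3.3 has "Eye movements during the intervention in group 1: standardised exercises, each at the end of week 1-4", and objective 4 in section 2.3 has eye movements "measured once a week in the intervention group over the intervention period". Section 4.3.3.1.1 speaks of the participants without naming a group. The secondary hypotheses in sections 2.4 and 2.5 compare the groups on eye movements during training items.

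**The concern.** The protocol recognises three sources of side effects (therapy, tests, glasses) but gives the assessor only one cause to accept or reject. This has two consequences.

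First, a reaction to a test, or to the glasses at baseline or post-intervention testing, is related to the study but has no class that says so.

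Second, where the glasses are worn inside a training session, dizziness has two named causes acting at the same time. Section 4.5.1.5 can assign it to the training on timing alone. If only group 1 wears the glasses in sessions, a measuring device is confounded with the gaze training under study.

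At stake is how the pilot's side effects are interpreted. Feasibility criterion (d) in section 4.4.14.1 judges the safety of the intervention from them, as a basis for a larger trial. The adverse-event definitions are set in the protocol and steer what is collected, so later analysis could repair the gap only in part.

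**Working it through.** **Classification, rule by rule.** Take dizziness that begins while glasses are worn in a group 1 session.

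- Section 4.5.1.2 read strictly: if the glasses caused it, there is no causality to the therapy, so it is an adverse event but not a side effect.
- Section 4.5.1.5, treatment-associated: the alternatives are joined by *or*, and a temporal relationship to the intervention is one of them. The event arose during the session, so it qualifies.
- Section 4.5.1.5, non-therapy associated: again joined by *or*, and absence of reasonable suspicion against the intervention is enough. If the doctor blames the glasses, the event qualifies here too.

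The same event meets both definitions. The log items do not include whether glasses were worn. A reaction to a test, or to the glasses at testing, can only be called unrelated or, on timing, be put down to the therapy.

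**Overlap of causes.** Section 4.4.15 places the measurement in the last session of each week, during exercises 2, 3, 4, 6 and 7. In the intervention-group manual, exercises 2 and 4 are head rotation and head flexion/extension with gaze targets.

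**Exposure.** Inputs: 34 participants, 17 per group (section 4.1.2.3); 16 sessions of 30 minutes (4.2.1); glasses for 12 minutes once a week in training and about 5 minutes at each of two assessments (4.3.3.1.3). The plan's sample size reproduces: 30 / (1 - 0.10) = 33.3, rounded up to 34.

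- Group 1 per patient: 4 x 12 + 2 x 5 = 58 minutes.
- Group 2 per patient, under Table 2 and objective 4: 2 x 5 = 10 minutes.
- In-session wearings: 17 x 4 = 68 against 0.
- Share of group 1 training: 4/16 = 25% of sessions; 48/480 = 10% of minutes.
- If section 4.3.3.1.1 applies to everyone: 58 against 58 minutes, and no arm imbalance.

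**Illustration.** The documents give no dizziness rate, so p per wearing is an assumption. Expected device events in group 1 sessions are 68p; the chance of at least one is 1 - (1 - p)^68, assuming full attendance and independent wearings.

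- p = 0.5%: 0.34 expected; 29%.
- p = 1%: 0.68 expected; 50%.
- p = 2%: 1.36 expected; 75%.
- p = 5%: 3.4 expected; 97%.

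With 15 completers per group (30 / 2) there are 15 x 4 = 60 wearings, and the chance runs from 26% at p = 0.5% to 95% at p = 5%. These are device events, not misclassified events; the misclassified share depends on the assessor.

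**The case against.** A reader might infer that the protocol charges gaze training with every dizzy spell caused by the glasses. The documents do not support that. Section 4.5.1.2 taken alone points the other way, section 4.5.1.5 also offers the non-therapy class, and a doctor must confirm the association (4.5.2.1.1). Misattribution is permitted, not prescribed.

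Nor are serious reactions to tests lost. Section 4.5.1.3 applies seriousness to adverse events and side effects alike, and causality only selects the label. Section 4.5.2 has all events recorded, and sections 4.5.3.1 and 4.5.3.2 require every serious incident to be reported within the same time.

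A reader might also infer that criterion (d) would fail. It is not a rate, and it tolerates very mild, transient effects. The reaction named for the glasses is temporary dizziness, after which they are switched off and removed. Section 5.6.1 plans adverse events as descriptive counts, and the protocol plans no between-group test of them.

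The one-arm premise is not settled either: section 4.3.3.1.1, synopsis item 2.11 and the secondary hypotheses do not confine in-session wearing to group 1. Finally, part of the information may be recoverable, because wearing happens at a fixed point and the log asks for the beginning and end of each event. Recovery is uncertain: the glasses cover only 12 of 30 minutes, and the protocol does not say how finely onset is timed.

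All of this limits the size of the point. It does not remove the missing category or the rule by which one event fits both causality classes.

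**Conclusion.** The point holds as a defect in attribution. The protocol names tests and glasses as causes of side effects but provides no class for them, and section 4.5.1.5 lets in-session glasses dizziness be filed as treatment-associated or as non-therapy associated.

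Under objective 4 and Table 2 the device and the gaze training are confounded in group 1, with up to 68 in-session wearings against 0 and 58 against 10 minutes per patient. If both groups wear the glasses, the imbalance disappears and the missing category remains.

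The 0.3 to 3.4 expected device events rest on an assumed 0.5% to 5% per wearing, full attendance and independence. The harm is to the interpretation of side effects; temporary dizziness alone would probably not change the outcome of criterion (d). The change is still worth making before data collection because it is cheap and hard to reconstruct afterwards.

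**What to change.** 1. In sections 4.5.1.2, 4.5.1.3 and 4.5.1.5, relate causality to the study intervention or a study procedure (tests, eye-tracking glasses), and record the suspected cause separately as training, test or glasses. Carry this into the assessment in 4.5.2.1.1 and correct the slip in the opening words of 4.5.1.2.
2. In section 4.5.1.5, do not let a temporal relationship alone assign an event to the training when it began while glasses were worn.
3. Add a yes/no item to the log in 4.5.2.1.2 for whether glasses were worn at onset.
4. Report side effects for criterion (d) and by group, with and without events that began while glasses were worn. Treat the glasses-free sessions as a sensitivity view, not a clean rate: glasses are always worn in the last session of the week, while section 1.3 expects training dizziness initially.
5. Reconcile sections 2.3 and Table 2 with sections 4.3.3.1.1, 2.4 and 2.5 on which group wears the glasses in sessions.

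The cost is wording in a few definitions, two log items and an extra table row, with slightly more log work. Sample size is unaffected.
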